## Abstract

**Background:**

*Post-operative cognitive dysfunction* (POCD) is an overarching term used to describe cognitive impairment identified in the preoperative or post-operative period. After surgical operations, older patients are particularly vulnerable to memory disturbances and other types of cognitive impairment. However, the pathogenesis of POCD remains unclear with no confirmed preventable or treatable strategy available. Our previous study demonstrated that the concentration of choline acetyl transferase in the cerebral spinal fluid was a predictive factor of POCD and that donepezil, which is an acetylcholinesterase inhibitor used in clinical settings for the treatment of Alzheimer’s disease, can prevent learning and memory impairment after anaesthesia/surgery in aged mice. This study aimed to determine the critical role of donepezil in preventing cognitive impairment in elderly patients undergoing orthopaedic surgery.

**Methods:**

A multicentre, double-blind, placebo-controlled, crossover clinical trial will be performed to assess the efficacy of donepezil in elderly patients undergoing orthopaedic surgery. Participants (*n* = 360) will receive donepezil (5 mg once daily) or placebo from 1 day prior to surgery until 5 days after surgery. Neuropsychological tests will be measured at 1 day before the operation and 1 week, 1 month, 6 months and 1 year after the operation.

**Discussion:**

This research project mainly aimed to study the effects of donepezil in elderly patients undergoing orthopaedic surgery due to underlying POCD and to investigate the underlying physiological and neurobiological mechanisms of these effects. The results may provide important implications for the development of effective interfering strategies, specifically regarding cognitive dysfunction therapy using drugs.

**Trial registration:**

ClinicalTrials.govNCT04423276. Registered on 14 June 2020

**Supplementary Information:**

The online version contains supplementary material available at 10.1186/s13063-021-05648-0.

## Background

Post-operative cognitive dysfunction (POCD) has been described as an objectively measurable decline in cognitive function at varying intervals after anaesthesia and surgery, up to 3 months to 7.5 years after surgery [1, 2]. Severely affected individuals may experience personality changes and a reduced capacity for social interaction. Some patients even develop irreversible cognitive impairment [3]. Monk et al. reported that POCD leads to increased mortality in the first year after surgery [4]. Steinmetz et al. not only confirmed the results by Monk et al. but also showed that POCD after noncardiac surgery is highly associated with the risk of leaving the labour force prematurely [5]. The incidence of POCD in patients older than 60 years at discharge has been reported to be 41.4% [6]. The incidence of POCD at 7 days after lower extremity joint replacement is as high as 41–75% [7]. As a serious post-operative complication, POCD can lead to a longer bed time of patients and increase the incidence of pressure ulcers, severe pulmonary infection and lower extremity deep vein thrombosis. At the same time, patients are not conscious and cannot effectively cooperate with examination and treatment in the hospital, and post-operative rehabilitation is also greatly reduced, even leading to surgery failure. In addition, if POCD is not alleviated for a long time, hospitalisation time and cost greatly increases, and it may be life-threatening in severe cases [8–10]. However, the aetiology and mechanism of POCD remain elusive.

The cholinergic system of the central nervous system is widely considered to be essential in learning and memory, including the modulation of the acquisition, encoding, consolidation, reconsolidation, extinction and the retrieval of memory [11]. This system degenerates during ageing and in neurodegenerative diseases such as Alzheimer’s disease (AD) [11, 12]. In the normal human hippocampus, a striking and highly significant age-related decline in choline acetyltransferase (ChAT) occurs from middle to old age (between 40 and 100 years) [12]. Cholinesterase inhibitors are now commonly used to improve cognitive function in patients with AD and related dementias by enhancing central cholinergic transmission [13]. Donepezil is a highly selective and reversible acetylcholinesterase inhibitor that improves cognition and memory of mild to moderate AD in patients by increasing the concentration of acetylcholine at the neuronal synaptic cleft [14–17]. Our previous animal study demonstrated that donepezil administration prevents isoflurane-induced learning and memory impairment in aged mice [18, 19], and our clinical study showed that lower preoperative CSF levels of ChAT and ACh can predict POCD occurrence at 7 days in aged patients [20]. In a pilot study, Doraiswamy demonstrated that donepezil improved some aspects of memory in terms of cognitive decline after coronary artery bypass [21]. Therefore, a randomised controlled trial is indicated to assess the efficacy of donepezil with regard to reducing the occurrence rate of POCD among elderly patients undergoing orthopaedic surgery.

## Aims and objectives

We aim to investigate the effect of donepezil on the improvement of cognitive function in elderly patients undergoing orthopaedic surgery. Our primary objective is to evaluate the incidence of POCD 7 days (or before leaving hospital) after surgery. Our secondary objective is to evaluate the incidence of POCD at 1 month, 6 months and 1 year after surgery and post-operative delirium during the hospital stay. We predict that the donepezil intervention will alleviate post-operative cognitive impairment in elderly patients undergoing orthopaedic surgery. We aim to provide reliable clinical evidence for reducing the rate of POCD.

## Trial design

This is a protocol for a multicentre, double-blind, randomised, two-arm parallel-group, placebo-controlled, interventional clinical study. We will observe the effects of the perioperative administration of donepezil on the post-operative cognitive function of elderly patients undergoing orthopaedic surgery.

This study was presented according to the recommendations of the Standard Protocol Items: Recommendations for Interventional Trials (SPIRIT) (supplemental file, SPIRIT checklist). The study was registered on the ClinicalTrials.gov (No. NCT04423276) on 14 June 2020. The trial registration data set is presented in supplemental table.

## Methods

### Participants, interventions and outcomes

#### Study setting

This study will enrol approximately 360 participants from the Renji Hospital Shanghai Jiao Tong University School of Medicine, Tenth People’s Hospital of Tongji University and Shanghai Guanghua Hospital of Integrated Traditional Chinese and Western Medicine. This clinical trial has been approved and supported by the ethics committee of the Renji Hospital Shanghai Jiao Tong University School of Medicine (RJ17189).

#### Eligibility criteria

Patients will be recruited primarily from three centres. Table 1 presents a summary of the inclusion and exclusion criteria.

**Table 1 Tab1:** Inclusion/exclusion criteria

Inclusion criteria	Exclusion criteria
1) Elder than 60 years old 2) Speak Chinese Mandarin 3) Scheduled to undergo hip or knee replacement surgery 4) The operation time is more than 2 h 5) Signed the inform consent 6) American Society of Anesthesiologists (ASA) classification I–II	1) Existing cerebral disease, or have a history of neurological and psychiatric diseases including Alzheimer Disease, stroke, epilepsy and psychosis 2) Existing cognitive impairment as evidenced by Mini-Mental State Examination scores below 24 3) Several audition or vision disorder 4) Patients with tumours or infections 5) Unwillingness to comply with the protocol or procedures 6) Cannot communicate normally in Mandarin Chinese 7) Existing bradycardiac arrhythmia (Heart rate <60 bpm for any reasons) 8) Existing gastrointestinal ulcer 9) Existing urinary incontinence 10) Existing asthma or chronic obstructive pulmonary disease 11) Post-operative admission to ICU 12) Allergic to donepezil

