#### Recruitment and informed consent

Figure 1 presents the schedule of the major study events for each study visit. Elderly patients who are scheduled to undergo orthopaedic surgery will be included in this study. This study is approved by the Ethics Committee of Ren Ji Hospital, Shanghai Jiao Tong University School of Medicine. Surgery will be performed within 2 days after the screening process. Designated doctors will explain this trial to interested potential participants in detail and provide them with the informed consent form. Participants are given at least 24h to decide whether they wish to participate in this trial. The informed consent form will be signed by the participant or his/her trustee or guardian and may be withdrawn at any time during the trial. Written informed consent and the patient’s baseline data will be obtained before randomisation. Moreover, participants are encouraged to contact the research team if they have any health concerns during the trial. Recruitment and consenting of study participants by the members of the research team is in-line with good clinical practice (GCP). During the clinical trial, the researchers will immediately report any serious adverse events occurring in the subjects, whether related to the drug under study or not, to the director in charge of the clinical trial of the research institution and contact [name] or [name].

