#### Allocation

Subjects will be randomly assigned to one of the following two groups: donepezil group or control group (placebo). Randomisation will be performed as a block randomisation, stratified by the centre with 1:1 allocation, using SAS software. A random code will be generated between the donepezil group and the control group from each centre, in a 1:1 ratio. Envelopes containing the random codes will be generated and distributed to each centre. Drugs will be allocated according to these random numbers by personnel who are unrelated to the trial, and a code will be assigned to each drug. Upon entering the study, each subject will be assigned to either the donepezil group or the control group with an equal probability according to the random code at each centre.

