#### Intervention

Subjects will receive 5 mg of donepezil or placebo once every night starting from 1 day before surgery until 5 days after surgery. On the day of surgery, patients will have a peripheral vein opened as a routine procedure. After measuring pulse oximetry, electrocardiogram and noninvasive blood pressure, general anaesthesia will be induced with 0.05 mg/kg midazolam, 1 mg/kg propofol, 0.6 mg/kg rocuronium and 0.5 μg/kg sufentanyl. Anaesthesia will be maintained with intravenous cisatracurium, sevoflurane, remifentanil and propofol. The drug dosage will be adjusted according to the patients’ hemodynamic response to maintain stable haemodynamics. To ensure that the patient’s haemoglobin level remains > 8 g/dL, blood will be transfused when the haemoglobin level drops to < 8 g/dL. Succinylcholine will be avoided during surgery. Post-operative analgesia will be given through patient-controlled intravenous analgesia. Patients will be returned to the general ward once they recover from anaesthesia.

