### Methods in analysis to handle protocol non-adherence and any statistical methods to handle missing data

The statistical analysis will be conducted on an intention-to-treat (ITT) basis. The analyses of the outcomes will be analysed as randomised, regardless of protocol adherence. All variables will be screened for frequency and type of missingness. Multiple imputation will be used if missingness is above 5% in any variable. In the case of missing data and imputation, complete case analysis will be performed as a sensitivity analysis.

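### Exclusion criterion 11, ICU admission after surgery, can only occur after randomisation and first dose, and conflicts with the as-randomised ITT analysis

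*Protocol article*

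**What the plan says.** In the protocol article, Table 1 (Eligibility criteria) includes "11) Post-operative admission to ICU" among the exclusions. Its inclusion list has "4) The operation time is more than 2 h" next to a criterion that is worded prospectively, "Scheduled to undergo hip or knee replacement surgery".

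Three sections fix the timing:

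- Recruitment and informed consent: consent and "baseline data will be obtained before randomisation".
- Allocation: "Upon entering the study, each subject will be assigned to either the donepezil group or the control group with an equal probability".
- Intervention: capsules are taken "once every night starting from 1 day before surgery until 5 days after surgery".

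The section on non-adherence and missing data adopts intention-to-treat and adds: "The analyses of the outcomes will be analysed as randomised, regardless of protocol adherence". It plans multiple imputation when more than 5% of a variable is missing, with a complete-case sensitivity analysis.

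**The concern.** An eligibility criterion should be decidable before allocation. Criterion 11 is not, because it names something that happens after the operation, when the patient has already been randomised and has started study drug. If centres apply it, randomised patients leave the trial because of a post-treatment event. If the ITT rule is followed, the criterion has no effect.

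What is at stake is the primary comparison. ICU admission could plausibly be affected by study drug: Table 1 itself excludes patients with bradycardia, asthma or chronic obstructive pulmonary disease, though it gives no reasons. ICU admission is also plausibly related to POCD. Selecting on such an event gives up the protection of randomisation. It also leaves the primary analysis set open to two readings, and the choice between them could be made after outcomes are known.

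**Working it through.** **Step 1: order of events.** Consent and baseline come first, then randomisation at study entry, then the first capsule one day before surgery, then surgery, then any ICU admission. No reading of the Allocation and Intervention sections lets criterion 11 be checked before randomisation. Exclusions 7 to 10 are each worded as existing conditions and can be checked at screening. Criterion 11 has no such word, nor one such as planned or expected.

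**Step 2: the two statements side by side.** Table 1 makes post-operative ICU admission a reason for exclusion. The analysis section keeps everyone as randomised. Nothing in the article says how a randomised patient who goes to ICU is handled or analysed.

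**Step 3: what exclusion could do to the primary comparison.** The plan gives no figure of its own for this, so the calculation is an illustration.

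Inputs from the Sample size section:

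- control POCD rate *p* = 25%
- target 12.5%, a difference of 25 − 12.5 = 12.5 percentage points

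Assumed inputs (the documents give none):

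- no true effect, so *p* = 25% in both arms
- POCD among ICU patients *q* = 50% or 75%, the same in both arms
- ICU rates *r* by arm as shown in the table

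The POCD rate left in an arm after ICU patients are removed is (*p* − *r* × *q*) / (1 − *r*).

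Worked example, 7% vs 3% with *q* = 50%:

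- arm with 7% ICU: (0.25 − 0.07 × 0.50) / 0.93 = 0.215 / 0.93 = 23.12%
- arm with 3% ICU: (0.25 − 0.03 × 0.50) / 0.97 = 0.235 / 0.97 = 24.23%
- spurious difference: 1.11 points in favour of the arm with more ICU admissions

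| ICU rates | *q* = 50% | *q* = 75% |
|---|---|---|
| 5% vs 5% | 23.68 vs 23.68: 0 | 22.37 vs 22.37: 0 |
| 2% vs 1% | 24.49 vs 24.75: 0.26 points | 23.98 vs 24.49: 0.52 points |
| 7% vs 3% | 23.12 vs 24.23: 1.11 points | 21.24 vs 23.45: 2.22 points |

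The arm with more ICU admissions always looks better, because it loses more of its high-risk patients. If that arm is donepezil, the bias favours donepezil. If it is placebo, the same amount counts against donepezil.

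**The case against.** The strongest reply is that the article never says these patients are removed from the analysis. It commits to ITT, and its section on modifications and adherence allows the intervention to be discontinued only at the participant's request. A patient who later goes to ICU could simply be a deviation kept in the analysis. Table 1 is also called a summary, and the full protocol may be clearer. This stands in part: one cannot conclude that randomised patients will be dropped. But the reply works only if criterion 11 does nothing, and an investigator working from Table 1 would not know that. This is a conflict between two things the article states, not a detail left to a fuller document.

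A reader might go further in three directions that the documents do not support:

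- **Operation time as an equal defect.** Criterion 4 does not say expected, but it sits in an inclusion list used at screening and is naturally read as expected duration. It needs a clarifying word, no more.
- **A material loss of power.** The documents give no distribution of operation times and do not say that short operations are removed. The planned 360 also exceeds what the stated 10% dropout requires (300 / 0.9 = 334). After 10% dropout, 360 × 0.9 = 324 remain, 24 above the 300 required. No power loss can be claimed.
- **A bias that flatters donepezil and hides harm.** Direction depends on unknown ICU rates. Low rates are plausible in ASA I-II patients for whom return to the general ward is planned. The recruitment section requires immediate reporting of every serious adverse event, whether or not related to study drug, so exclusion from an efficacy analysis would not erase those reports.

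**Conclusion.** The point holds for criterion 11. It can be applied only to randomised, dosed patients, and applying it is incompatible with analysing everyone as randomised. The article leaves open which statement governs. This conclusion rests on the text alone and needs no assumed number.

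The size of any bias is not known. Across the assumed unequal ICU rates it runs from about 0.3 to 2.2 points, roughly 2% to 18% of the 12.5-point target (0.26 / 12.5 and 2.22 / 12.5), with either sign. It is zero when ICU rates are equal. These figures assume no true effect and the same POCD rate among ICU patients in both arms. They show that the distortion would probably be modest, but it is avoidable and could not be corrected by analysing only the patients who were kept.

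**What to change.** Reconcile Table 1 with the analysis section:

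- Delete criterion 11, or limit it to ICU admission already planned before randomisation.
- State that every randomised patient stays in the ITT set whatever happens after surgery, and that patients who cannot be tested fall under the existing missing-data rules.
- Report unplanned ICU admission by arm.
- As a minor clarification, word criterion 4 as expected operation time, judged before randomisation.

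The cost is a short text amendment and no extra patients. The downside is that some ICU patients will be hard to test at day 7, so their primary outcome will have to be imputed.

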#### Recruitment and informed consent

Figure 1 presents the schedule of the major study events for each study visit. Elderly patients who are scheduled to undergo orthopaedic surgery will be included in this study. This study is approved by the Ethics Committee of Ren Ji Hospital, Shanghai Jiao Tong University School of Medicine. Surgery will be performed within 2 days after the screening process. Designated doctors will explain this trial to interested potential participants in detail and provide them with the informed consent form. Participants are given at least 24h to decide whether they wish to participate in this trial. The informed consent form will be signed by the participant or his/her trustee or guardian and may be withdrawn at any time during the trial. Written informed consent and the patient’s baseline data will be obtained before randomisation. Moreover, participants are encouraged to contact the research team if they have any health concerns during the trial. Recruitment and consenting of study participants by the members of the research team is in-line with good clinical practice (GCP). During the clinical trial, the researchers will immediately report any serious adverse events occurring in the subjects, whether related to the drug under study or not, to the director in charge of the clinical trial of the research institution and contact [name] or [name].

**Fig. 1 Fig1:**
[figure not shown]
Schedule of the major study events

#### Allocation

Subjects will be randomly assigned to one of the following two groups: donepezil group or control group (placebo). Randomisation will be performed as a block randomisation, stratified by the centre with 1:1 allocation, using SAS software. A random code will be generated between the donepezil group and the control group from each centre, in a 1:1 ratio. Envelopes containing the random codes will be generated and distributed to each centre. Drugs will be allocated according to these random numbers by personnel who are unrelated to the trial, and a code will be assigned to each drug. Upon entering the study, each subject will be assigned to either the donepezil group or the control group with an equal probability according to the random code at each centre.

#### Intervention

Subjects will receive 5 mg of donepezil or placebo once every night starting from 1 day before surgery until 5 days after surgery. On the day of surgery, patients will have a peripheral vein opened as a routine procedure. After measuring pulse oximetry, electrocardiogram and noninvasive blood pressure, general anaesthesia will be induced with 0.05 mg/kg midazolam, 1 mg/kg propofol, 0.6 mg/kg rocuronium and 0.5 μg/kg sufentanyl. Anaesthesia will be maintained with intravenous cisatracurium, sevoflurane, remifentanil and propofol. The drug dosage will be adjusted according to the patients’ hemodynamic response to maintain stable haemodynamics. To ensure that the patient’s haemoglobin level remains > 8 g/dL, blood will be transfused when the haemoglobin level drops to < 8 g/dL. Succinylcholine will be avoided during surgery. Post-operative analgesia will be given through patient-controlled intravenous analgesia. Patients will be returned to the general ward once they recover from anaesthesia.

### Interventions, modifications, adherence and concomitant care

The assigned intervention will be discontinued only in response to participant request. No modification of the interventions is planned during the trial. Adherence to interventions mainly refers to patient self-management adherence. No concomitant care or interventions are permitted during this trial.

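### The article makes participant request the sole ground for stopping study drug, which as worded excludes an investigator-led stop for safety

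*Protocol article*

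**What the plan says.** The section on interventions, modifications, adherence and concomitant care sets the stopping rule: "The assigned intervention will be discontinued only in response to participant request". The next sentence adds: "No modification of the interventions is planned during the trial".

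The Intervention section has donepezil 5 mg or placebo given nightly from the day before surgery to the fifth day after it.

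Table 1, under Eligibility criteria, bars entry for, among other things, "Existing bradycardiac arrhythmia (Heart rate <60 bpm for any reasons"), "Existing gastrointestinal ulcer" and "Allergic to donepezil". It also lists post-operative ICU admission as an exclusion.

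On safety handling, the section on recruitment and informed consent says that "the researchers will immediately report any serious adverse events occurring in the subjects", with the report going to the director in charge of the trial at the institution. It also lets consent be withdrawn at any time. Unblinding procedures allows an emergency envelope to be opened. The section on adverse events and harms promises an evaluation of harm from the intervention.

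**The concern.** The difficulty is the word *only*. A condensed article may leave its list of stopping criteria to the full protocol, and silence would not be a finding. This sentence is not silent: it states a closed rule with one trigger. A dose hold or reduction is not offered as an alternative, since no modification is planned.

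Two features of this trial make a request-only rule weak.

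- The trial screens out patients with certain conditions at entry, and some of these can develop after the first dose. The article gives no matching on-treatment stop.
- Dosing runs through the first post-operative days in patients over 60, and delirium in hospital is a secondary outcome. A patient who is inattentive or has altered consciousness may not be able to ask for the drug to be stopped. The stopping rule names the participant and does not mention a representative.

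At stake is patient safety during the dosing week, and whether an investigator who does stop the drug has acted within the protocol or departed from it.

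**Working it through.** The article has no figure to reproduce on this point. The check sets the stopping rule beside every other section that touches safety, withdrawal or monitoring, and asks of each: does it let the investigator stop study drug?

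- **Recruitment and informed consent.** Serious adverse events are reported immediately, whether or not related to the drug. Consent, signed by the participant or a trustee or guardian, can be withdrawn. The first is a reporting duty. The second is a route out on the participant's side. Neither is an investigator's decision to stop.
- **Eligibility criteria, Table 1, exclusion 11 (post-operative ICU admission).** Dosing starts before surgery, so this can apply only once dosing has begun, and it does not depend on the participant's request. It concerns eligibility and covers one situation. It does not say what happens to study drug.
- **Unblinding procedures.** The investigator may learn the allocation in a medical emergency and must document why. No action on study drug follows in the text. Serious adverse events are also recorded for analysis when the trial ends.
- **Adverse event reporting and harms.** Harm will be evaluated, and the case report form has space for unexpected side-effects. Collection is non-systematic. No action on study drug is stated.
- **Data-monitoring committee; Interim analyses.** There is no committee and no formal interim analysis, so no stop arises from either.
- **Provisions for posttrial care.** Free treatment is offered for research-related injury. This does not concern stopping the drug.
- **Non-adherence and missing data.** Patients are analysed by intention to treat whatever their adherence. The section gives no ground for stopping, but the analysis can absorb stops without change.

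The answer is no for each section. The part of the article between the section on non-adherence and missing data and Dissemination plans was not available, so the statement covers the text that was read.

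**Which entry conditions can first appear on drug.** A heart rate below 60 bpm, a gastrointestinal ulcer and an allergic reaction to donepezil can each arise within a dosing week. That this calls for a stop is a clinical inference: Table 1 gives no reasons for its exclusions.

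**Exposure under the rule.** Inputs: 5 mg nightly from day −1 to day +5 (Intervention section), and about 360 patients (Study setting; Sample size).

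- Doses: days −1, 0, 1, 2, 3, 4, 5 = 7.
- Total dose on the donepezil arm: 7 × 5 mg = 35 mg.
- Rate of events needing a stop, or of patients unable to ask: not given, and none assumed. The 25% incidence in the sample size section is for POCD, assessed at about 7 days. It is not a rate of patients unable to make a request.

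**The case against.** The strongest reply is that no clinician would keep giving a capsule to a patient in trouble because of one sentence in a journal article. The safety sections point the same way. Serious events go at once to the director in charge of the trial. Unblinding is reserved for emergencies in which the allocation has to be known, which makes sense only if clinical action may follow. Harm is to be evaluated. ICU admission shows that the authors foresaw a clinical event affecting the place of an already dosed patient. The article describes adverse effects as minor and the drug as generally well tolerated, and the course is 7 doses.

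Most of this stands and limits the size of the point. It does not remove it. None of these provisions says the drug may be stopped, and none overrides *only*. A clinician who stops the drug would be doing the sensible thing against the stated rule.

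A reader might also infer more than the text supports:

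- **That the trial has no safety stop at all.** The full protocol is not shown and may contain one. In that case the published sentence contradicts it and still needs correcting.
- **That patients will in fact be kept on drug through adverse events.** The documents describe a rule, not conduct, and give no event rate.
- **That every entry exclusion should become a stopping criterion.** Some cannot: chronic obstructive pulmonary disease, for example, will not newly arise within 7 nightly doses. A count of exclusions would measure no risk.
- **That the same section's ban on concomitant care prevents treatment of complications.** The Intervention section prescribes transfusion and analgesia, and the posttrial care section promises treatment for injury. The breadth of that sentence is a separate drafting matter and forms no part of this point.

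**Conclusion.** The point holds as a patient-safety defect in wording. As published, the participant's request is the sole ground for stopping study drug, and nothing in the available text gives the investigator a safety stop. The rule applies to about 360 patients, each for 7 nightly doses (35 mg in total on donepezil).

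The conclusion rests on reading *only* in its ordinary sense and on the absence of any overriding text in the one part of the article that could not be read. It does not rest on any assumed frequency of bradycardia, ulcer, allergy or delirium.

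A reader might infer that the statistical result is threatened. It is not: the sample size, the primary comparison and the intention-to-treat rule are unaffected. The sentence should be corrected because the correction is simple and the wording is wrong whether or not the full protocol contains safety stops.

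**What to change.** Replace the stopping sentence with, for example: *Study drug may be stopped at the request of the participant or their representative, or by the investigator for an adverse event, an emerging contraindication or a medical emergency requiring unblinding; the patient stays in follow-up and in the ITT analysis.*

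If the full protocol already has stopping criteria, bring the article into line with them.

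The cost is one sentence, passed through the ethics committee review that the article requires for any protocol change. Randomisation, sample size, primary test and analysis set stay as they are, because patients are already analysed in their allocated group irrespective of adherence.
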